### Study variables

There will be three outcome variables:Knowledge of sexually transmitted infections as measured by the scale validated in Mexican teens by Robles-Montijo and Diaz-Loving [27]. This scale consists of 23 items with a response format “true”, “false” and I don’t know”. The sum of correct answers ranges from 0 (absence of knowledge) to 23 (high knowledge).Attitudes regarding condom use will be measured by the UCLA Multidimensional Condom Attitudes Scale [28]. This scale consists of 25 items and assesses five independent factors: (i) reliability and effectiveness of condoms, (ii) pleasure associated with condom use, (iii) stigma attached to being a condom user, (iv) embarrassment associated with the negotiation and use of a condom, and (v) embarrassment associated with the purchase of a condom. The scale was previously validated in Mexico [29] and has a Likert-type response format with values ranging from 1 (strongly disagree) to 7 (strongly agree) and with an intermediate value of 4 (undecided). Some questions are worded negatively indicating a negative attitude, so the score has to be reversed. Each domain is scored separately producing a score per domain. The domain rating is calculated as the sum of the items in the domain.Self-efficacy toward consistent condom use will be assessed by the seven measures proposed by Fishbein and colleagues [30] and then translated into Mexican Spanish by Robles-Montijo & Diaz-Loving [27]. These include one direct and six indirect measures toward consistent condom use. The direct measure will be obtained by the response to the item ‘Many different things can get in the way of using a condom when people have sex. How sure are you that you can use a condom every time you have vaginal sex with your main partner?’ The response is coded on a 1–7 Likert scale with ‘very sure I cannot’ and ‘very sure I can’ as endpoints. The indirect measure of self-efficacy toward consistent condom use will be obtained using six items. The first five had the commonality of ‘how sure are you that you can (could) always use a condom for vaginal sex?’ The conditions were: (1) when he/she has been drinking or using drugs, (2) when you have been drinking or using drugs, (3) when he/she is very sexually excited, (4) when you are very sexually excited, and (5) when he/she does not feel like using a condom. The final item is focused on an abstinence self-efficacy: ‘what if you and your main partner want to have sex and a condom is not available? How sure are you that you can put off having vaginal sex with your main partner until you or he/she can get one?’ All responses to indirect measures are on a 0─10 scale format where 0 indicated ‘absolutely sure you cannot’ and 10 ‘absolutely sure you can’ [30].

We will also measure and statistically control for covariates related to teens’ preventive behaviors. These covariates include parental characteristics such as parental education, occupation, family structure and parental communication about risky sexual behaviors; information on risky sexual behaviors obtained through the mass media in the 3 months prior to each study evaluation, and the teens’ general characteristics such as sex, age, school performance (average grade point for the past year), substance use (tobacco, alcohol and drugs) and social desirability.

Parental communication about risky sexual behaviors will be measured by the scale designed and validated in Mexican adolescents by Robles-Montijo & Diaz-Loving [27]. This scale has ten items, which reflect communication about sex, sexually transmitted infections, alcohol and drug consumption, unwanted pregnancy, use of birth control, abortion, and male and female condoms. Responses are coded on a 1─3 Likert format scale: 1 (never), 2 (occasionally) and 3 (always). The total sum score varies from 10 (no communication) to 30 (strong communication).

Social desirability will be measured with the “Lie scale” of the Eysenck Personality Questionnaire. This questionnaire measures three domains of personality (psychoticism, neuroticism and extroversion) and includes a social desirability or ‘Lie scale’ that measures attempts to answer in a socially desirable manner. The Lie scale consists of 20 items with dichotomous response format (Yes or No). The responses sum score ranges from 0 (low social desirability) to 20 (high social desirability). This scale was validated in Mexican children between 12 and 15 years of age [31].

Furthermore, we will also measure and compare (between intervention and control group) the variables related to the teen’s sexual behaviors. These behaviors include history of first intercourse, number of sexual partners, age of current or most recent sexual partner, time elapsed after the last intercourse, and condom use during the first and last intercourse. We did not consider these variables as outcomes because previous studies reported that only ~20 % of Mexican adolescents from the third year of secondary school are sexually active [32, 33] and because the primary objective of this study is to design an intervention to prevent risky sexual behaviors.

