### Description and evaluation of the intervention

The study materials are available on the Internet web page (http://tu-ssexual.com), which can be accessed with the participant e-mail address and a centrally assigned password.

The intervention will include an introduction and four educational sessions (Table 1) and will last 1 month (one session per week) followed by a 3-month follow-up. Teens will be allowed to access a weekly session at any time and as often as he/she likes. However, the sessions will be consecutive so teens will not be able to access to the subsequent session without completing the previous one. Each session has an average duration of 1 h and ends with overview questions. Additionally, at the end of each session, teens will be asked what they like and dislike about the session. Answers will be recorded in the study database.

**Table 1 Tab1:** Contents of the intervention

Session	Main topic	Contents
Introduction	Welcome	Welcome and general explanation of the organization of the website and instructions for its use.
		Invitation and compulsory automatic pass to answer the questionnaire that collects information on study variables.
1.	What I have to know before the first time or when it happened…?	1. What is dating? What is courtship? 2. Kisses, caresses and … what’s next? □ What is a sexual relationship? □ What is sexual pleasure? □ What is masturbation? □ What is sexual intercourse? □ Different sexual practices … 3. Having sex is the same for men as for women? 4. What should be a basis for a good relationship during courtship or dating? 5. How to recognize when your partner abuses you in order to not allow it (forms of abuse). 6. Self-esteem and its relation to self-care
2.	It is better to be informed and take care to prevent sexually transmitted infections	1. How sex can affect my health? Statistics of sexually transmitted infections (STIs) in adolescents in the world and in Mexico. 2. How can I realize when I or my partner has a sexually transmitted infection? 3. Are there medical tests to determine whether or not I have any type of sexually transmitted infection? 4. STIs affect women differently than men? 5. Are there vaccines to prevent STIs or treatments against them? 6. How I can protect myself from STIs? Ways to practice safe sex.

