3.	It's better to know and care regarding HIV/AIDS and unwanted pregnancy.	1. HIV/AIDS: 1.1 How HIV/AIDS affects health. 1.2 Statistics on the prevalence of HIV/AIDS worldwide and in Mexico. 1.3. Ways of transmission of HIV/AIDS. 1.4 Common symptoms of people with HIV/AIDS: 1.5 Methods of detection and protection. 2. Is there any other risk in addition to STIs? And what if I get pregnant? What if my girlfriend gets pregnant? Teenage pregnancy statistics. Contraceptive methods: pros and cons. 3. Steps to use male and female condoms
4.	Preparing for a pleasant and safe sexual experience. Am I ready?	1. How can I negotiate condom use? Learning strategies for condom use negotiation 2. Tips for condom negotiation: □ at first intercourse □ at intercourse with a stable and casual partner □ when one of the two consumed alcohol □ when both are very excited 3. Make your own comics about how you would negotiate using a condom with your partner 4. E-sites on sexual and reproductive health

Furthermore, during the intervention and follow-up, booster e-mail messages will be sent to the teens of the intervention group. “Booster messages” will emphasize the main points of the educational sections and will be sent two to three times per week from the second week of the intervention.

Information on the study variables will be obtained through the Internet-based self-applied questionnaire and collected on three occasions: 1) when the adolescent enters into the study (baseline), 2) once the intervention is completed (at 1 month) and 3) after 3 months of follow-up (fourth month).

In the control group, teens will continue the usual school-provided sex education and will be invited to answer the Internet-based self-applied questionnaire at the same time as the intervention group. Furthermore, at the conclusion of the study, teens from the control group will also receive access to the educational sessions.

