### Recruitment and retention strategies

To improve recruitment and retention of teens in the study, we will implement strategies focused on teens, their teachers and parents. Recruitment strategies will incorporate provision of information and reinforcement of the potential benefits of the intervention. Retention strategies will include the following: 1) e-mail reminders of each session; 2) placing reminders with brief thematic description of the weekly session in classrooms; 3) follow-up e-mail messages about technical and other problems regarding each learning session and solutions to such problems; 4) parent and teacher involvement in motivating adolescents’ participation.

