### Statistical analysis

The unit of analysis and inference will be an adolescent. Comparison of the characteristics of teens and their parents between intervention and control groups will be made using the chi-square test for categorical variables and Student t-test for continuous variables to describe the study population and ascertain similarity of both groups at baseline measure.

Scores for each outcome variable will be calculated according to the scoring algorithms. Differences in baseline and post-intervention stages for outcome variables will be compared within each group. Differences between groups will be compared using the differences-in-differences (D-in-D) estimator [34]. The generalized linear model (GLM) will be used to assess changes in each outcome variable controlling for baseline measures and study covariates. GLM methods allow for modeling the correlation of the repeated observations on the same subjects [35].

The analysis will be performed according to the intention-to-treat approach. Missing measurements due to a participant’s withdrawal from the study will be replaced with the most recent observations; p value <0.05 will be considered as statistically significant. The analysis will be performed using Stata v.11.0 statistical software (Stata 11.0, Stata Corp; College Station, TX).

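### Controlling for media information re-measured at months 1 and 4 could remove part of the intervention's own effect; the primary model should use entry values

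*Protocol article*

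**What the plan says.** The Study variables section introduces the adjustment set with "We will also measure and statistically control for covariates related to" preventive behaviours in teens. One member carries its own timing: "information on risky sexual behaviors obtained through the mass media in the 3 months prior to each study evaluation". The set also includes "family structure and parental communication about risky sexual behaviors", together with substance use and social desirability, but these have no such timing attached.

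Under Description and evaluation of the intervention, the intervention "will last 1 month (one session per week) followed by a 3-month follow-up". The same section states: "Information on the study variables will be obtained through the Internet-based self-applied questionnaire and collected on three occasions". The occasions are entry, month 1 and month 4. Booster e-mails go to the intervention group only, from the second week of the intervention and on through follow-up. Table 1 shows that the entry questionnaire is completed in the introduction, before session 1, and that session 4 includes "E-sites on sexual and reproductive health".

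The Statistical analysis section plans a difference-in-differences comparison and a generalized linear model for repeated observations, "controlling for baseline measures and study covariates". It declares an intention-to-treat approach. Nowhere are covariates restricted to entry values.

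**The concern.** A covariate recorded after the intervention has started may itself be a result of the intervention. Holding it fixed compares teens at equal media exposure, which takes out whatever the strategy achieved by changing that exposure. An intention-to-treat analysis of a strategy is normally meant to estimate its total effect, so the adjusted contrast would answer a different question. There is a second risk: where something unmeasured, such as interest in the topic, drives both later media use and the outcome, conditioning on later media use can create bias of its own.

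Difference-in-differences does not protect against this. It removes fixed differences between the schools, whereas the problem here is a covariate that may move differently in the two groups after baseline.

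**Working it through.** The plan gives no figure for this point. The check therefore has three parts: the timing, the algebra of adjustment, and a scale for the result.

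**1. What each look-back covers** (sessions run from month 0 to month 1)

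| Evaluation | Three-month window | Relation to the intervention |
|---|---|---|
| Entry | −3 to 0 | wholly before |
| Month 1 | −2 to 1 | two months before, one month of sessions |
| Month 4 | 1 to 4 | wholly after the sessions; boosters continue in one group |

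The entry and month-1 windows share 3 − 1 = 2 months, so the month-1 value mixes exposure before and during the sessions. Session 4 is the last weekly session, so on schedule its web sites could affect only about the last week of the month-1 window. They could affect the whole month-4 window. If teens count web content as media (the article does not define the item), the sessions themselves could also register at month 1.

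**2. What adjustment removes.** Work in SD units. Let a be the difference the intervention makes to the re-measured covariate (in difference-in-differences terms, the between-group difference in its change), and b the covariate's slope on the outcome at fixed group. Then

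total effect = direct effect + a × b,

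and the contrast adjusted for the re-measured value is total − a × b.

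The documents give neither a nor b. Assumed values:

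| a | b | Removed (SD) |
|---|---|---|
| 0 | any | 0 |
| 0.1 | 0.1 | 0.01 |
| 0.2 | 0.2 | 0.04 |
| 0.3 | 0.3 | 0.09 |
| 0.5 | 0.4 | 0.20 |
| 0.5 | 0.5 | 0.25 |

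A simulation with a = b = 0.3 and a direct effect of 0.41, hence a total of 0.41 + 0.3 × 0.3 = 0.50, returned 0.50 when adjusted for the baseline covariate value and 0.41 when adjusted for the re-measured value. That is 0.09 / 0.50 = 18% removed. The simulation had no unmeasured common cause, so it shows only the lost pathway and not the second bias.

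**3. Scale.** The Sample size section plans 200 teens per group with 25% drop-out: 200 × 0.75 = 150 completers per group. With two-sided alpha 0.05, 90% power (the plan's beta of 0.90 read as power) and independent observations, the detectable difference is (1.96 + 1.28) × √(2/150) = 3.24 × 0.1155 = 0.37 SD. Against that yardstick the middle case is 0.09 / 0.37, about a quarter. The 0.37 is derived here and is not a figure of the plan.

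**The case against.** **Which value enters the model is not stated outright.** The article says when media information is collected, not which time point is used, and an article may leave model detail to a fuller document. This stands as a limit on certainty. It does not dispose of the point: a controlled covariate is tied to each evaluation and named apart from baseline measures in a repeated-measures model, which makes the time-varying reading the natural one.

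**The other covariates.** A reader might infer that parental communication, substance use and social desirability are all adjusted at post-intervention values and all shifted by the intervention. The documents do not support that. Re-measurement follows only from the general sentence on the repeated questionnaire. The link to parents is "parent and teacher involvement in motivating adolescents" to take part; this is a retention measure, no group is stated, and nothing says that parents are asked to discuss sexual risk. No route is described for substance use or social desirability.

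**Month 4.** A reader might also take the month-4 look-back to cover the sessions. It does not; only the boosters and any later use of the listed sites fall within it.

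**Concurrent values have a use.** With two schools and no random allocation of teens, outside media exposure may diverge after baseline, and an entry value cannot capture that. The Discussion includes social desirability to correct self-report bias, which acts when the outcome is answered. Both arguments are fair, and they support keeping concurrent values as a sensitivity analysis.

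**Baseline main effects may do nothing.** In a linear difference-in-differences model on a balanced panel, baseline covariates entered only as main effects leave the group-by-time estimate unchanged. This is correct, so the fix must specify the form of adjustment.

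**Conclusion.** The point holds for media information. As written, the plan most naturally adjusts for a value that the intervention could change, and the resulting contrast would then not be the total effect of the strategy. For parental communication and any other changeable covariate in the repeated questionnaire, the same concern applies by inference only.

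The size is unknown. It is about a × b: zero if the intervention leaves media exposure unchanged, and 0.01 to 0.25 SD when a and b are each assumed to lie between 0.1 and 0.5. It would be wrong to conclude that the trial's estimate is biased by any particular amount, or that a material bias has been shown. The conclusion rests on three conditions: the re-measured value enters the model, the intervention shifts it, and it is related to the outcome. The first is the natural reading; the other two are plausible but not established. This is an avoidable weakness in the main estimate that should be corrected, not a fatal flaw.

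**What to change.** State that the primary model adjusts for media information, and for any other covariate that the intervention could change, at the values recorded at entry. Specify a form in which those values act on change: either a baseline-adjusted ANCOVA of the follow-up scores, or covariate-by-time terms in the difference-in-differences model.

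Use the month-1 and month-4 values only descriptively, or in an analysis labelled as sensitivity or mediation. Concurrent social desirability may be kept as a sensitivity adjustment for reporting bias.

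The cost is a short addition to the Statistical analysis section; no new data are needed. The downside is that the primary model no longer captures outside media differences between the two schools that arise after baseline. The sensitivity analysis with concurrent values addresses these, with the caveat that it may also remove part of the intervention's effect.

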### Sample size

Sample size was calculated using the software “A-priori Sample Size Calculator for Multiple Regression” (available at: http://www.danielsoper.com/statcalc3/calc.aspx?id=1). Effect of the intervention will be accessed by multiple regression analysis considering possible confounders due to the quasi-experimental nature of the study design. We considered the medium size effect for F-test (f2) of 0.15, alpha of 0.05, beta of 0.90, and 15 covariates. The number of teens by group, assuming a drop-out rate of 25 %, will be 200.

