## Methods

A field trial of one intervention and one comparison group with ex-ante and ex-post measurements will be conducted in two public secondary schools in the Iztapalapa Delegation in Mexico City. A delegation represents a geo-political area; Mexico City is divided into 16 delegations. Compared to the rest of the delegations, Iztapalapa has less favorable socioeconomic indicators [24]. The intervention will take place in one school and the second school will serve as a comparison group where we will observe the usual sex education being offered. The schools will be selected through simple random sampling from the list of public secondary schools in Iztapalapa. The study population will consist of adolescents between 14 and 15 years of age who are in the third year of secondary school and agree to participate through informed consent. Parents are also required to sign written informed consent.

The project was authorized by the National Research and Ethics Committee of the Mexican Institute of Social Security (R-2014-785-033), the Research and Ethics Committee of the Hospital Infantil de Mexico Federico Gómez (HIM 2015-066) and the General Directorate of Technical Secondary Education of the Secretary of Education.

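### The stated 200 per group does not follow from its own inputs, and those inputs describe a joint test of 15 predictors, not the planned intervention contrast

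*Protocol article*

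**What the plan says.** The Sample size section of the protocol article names its tool ("Sample size was calculated using the software “A-priori Sample Size Calculator for Multiple Regression") and says that the intervention effect will be judged by multiple regression with adjustment for confounders, because the design is quasi-experimental. The inputs stand in one sentence: "We considered the medium size effect for F-test (f2) of 0.15, alpha of 0.05, beta of 0.90, and 15 covariates". The result is "The number of teens by group, assuming a drop-out rate of 25 %, will be 200". No figure before drop-out is given, and no effect size is attached to the intervention term.

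The Methods section fixes two groups of one school each: "The intervention will take place in one school and the second school will serve as a comparison group". The Statistical analysis section makes the adolescent the unit of analysis. It plans a difference-in-differences estimate between groups, with a generalized linear model for each outcome adjusted for baseline and covariates. The Discussion repeats that the difference-in-differences estimator will sit inside that regression model.

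**The concern.** The section gives every input and the output, so the calculation can be checked, and the two do not agree. This is not a detail left to a fuller document.

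The second problem is the hypothesis. A calculator fed with f2 and "15 covariates" asks whether the whole set of predictors explains variance in the outcome. Parental education, sex, school grades and the other confounders could produce such a result with no intervention effect at all. The trial asks about one coefficient per outcome and post-baseline comparison. A reader of this section cannot learn what intervention effect the study can detect, and so cannot interpret a null result.

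Third, 0.90 is labelled beta. Taken literally, that would be 10% power.

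**Working it through.** **Inputs (all from Sample size):** f2 = 0.15; alpha = 0.05; power = 0.90 (printed as beta); 15 predictors; drop-out 25%; 200 per group, so 400 in total.

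**1. The plan's own calculation.** For the joint F-test, power = P(F′ > F crit), where F′ is noncentral F with df (15, N − 16) and noncentrality λ = f2 × N.

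- N = 170 gives power 0.8997; N = 171 (λ = 0.15 × 171 = 25.65, df 15 and 155) gives 0.902. The minimum is 171 in total.
- Drop-out as N/(1 − 0.25): 171/0.75 = 228, or 114 per group.
- Drop-out as N × 1.25: 171 × 1.25 = 213.75, so 214, or 107 per group.
- Reading 171 as per group: 214 or 228 per group.

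None of these is 200.

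**2. Other readings of the same inputs.**

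| Reading | N analysed | After 25% drop-out |
|---|---|---|
| λ = f2 × residual df | 185 | 232 to 247 |
| Beta of 0.90 taken literally (power 0.10) | 27 | 34 to 36 |
| 1-df test of one coefficient at f2 = 0.15 | 73 | 92 to 98 |

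Figures close to 200 appeared only when a stated input was changed. Examples are power 0.95 with no drop-out (199), 11 predictors with division by 0.75 (203), and 13 predictors with multiplication by 1.25 (203).

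**3. What the stated enrolment delivers.** 200 × 0.75 = 150 completers per school, 300 in total. Treating pupils as independent, the joint test at f2 = 0.15 has power 0.997, not 0.90.

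**4. The contrast that is planned.** For a 1-df test with 16 model terms (15 covariates plus intervention), df = (1, N − 17) and λ = f2 × N. The article gives no f2 for this term, so the values below are assumptions.

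| Assumed partial f2 | N needed for 90% power | Enrolled in total (N/0.75) | Power with 300 completers |
|---|---|---|---|
| 0.15 | 73 | 98 | >99.9% |
| 0.05 | 213 | 284 | 97% |
| 0.02 | 528 | 704 | 68% |
| 0.01 | 1053 | 1404 | 41% |

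With 300 completers, the smallest f2 detectable with 90% power is 0.0353. For equal groups, with the group indicator uncorrelated with the covariates, d = 2√f2 = 2 × √0.0353 ≈ 0.38 residual SD. On the same conversion, f2 = 0.15 is 2 × √0.15 = 0.77 residual SD.

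**5. The same on the raw-score scale.** For an unadjusted difference-in-differences with n = 150 per group and pre-post correlation r, SE = √(4(1 − r)/n) in raw SD units. The detectable difference is 3.2416 × SE, where 3.2416 is the sum of the normal quantiles for two-sided 0.05 and 90% power. The article gives no r, so a range is shown.

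| Assumed r | SE | Detectable difference (raw SD) |
|---|---|---|
| 0.3 | √(2.8/150) = 0.1366 | 0.44 |
| 0.5 | √(2.0/150) = 0.1155 | 0.37 |
| 0.7 | √(1.2/150) = 0.0894 | 0.29 |

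The closeness of 0.37 to the 0.38 in step 4 follows from choosing r = 0.5. The two are in different SD units and do not confirm each other.

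**The case against.** The strongest reply is that the error is harmless. If 200 per group means 400 in total, the plan enrols far more than the 214 to 228 its inputs require. At its own f2 of 0.15, both the joint test and the 1-df test exceed 90% power with 300 completers. That stands, as far as pupils can be treated as independent, and it limits the point to the justification rather than the enrolment.

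A second reply is that the article never says it sized a joint test. That is true: the reading rests on the calculator's name and on its inputs. But the 1-df reading, at 73 analysed and at most 98 enrolled, is further from 200. Neither reading makes 90% the power of the planned contrast.

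A third is that beta for power is a slip that misleads no one. This is fair; it needs correcting but adds little weight.

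Two stronger conclusions are tempting. A reader might infer that the trial is underpowered. The documents do not show this: on independent observations, power falls below 90% only if the intervention's own f2 is under about 0.035, and no expected effect is stated to compare with that.

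A reader might also apply a design effect for school and quote a larger detectable difference. No intraclass correlation is given. More fundamentally, with one school per arm there are no between-school degrees of freedom, so such a formula yields no valid power figure. Difference-in-differences removes school differences that are constant over time. Differential change between the two schools cannot be separated from the intervention effect, and no inflation of the sample would cure that.

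**Conclusion.** The point holds as a defect in the stated justification. The inputs give 107 to 114 per group (214 to 228 if 171 is taken per group) against the 200 printed, and the 90% does not describe the comparison the trial will make. The discrepancy runs towards over-enrolment, and no shortfall is established. The mismatch in numbers rests only on reading 0.90 as power. The mismatch in hypothesis rests on the reasonable inference that this tool with these inputs sizes the whole-set F-test. The detectable effects of 0.035 in f2 (about 0.38 residual SD), or 0.29 to 0.44 raw SD for r from 0.7 to 0.3, assume 25% drop-out, equal groups, independent pupils and no school-by-time variation.

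**What to change.** Keep 200 per group and rewrite the paragraph:

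- Remove the claim that 200 follows from f2 = 0.15 with 15 covariates.
- Replace beta with power.
- State the detectable effect for the 1-df intervention term. With 300 completers, two-sided alpha 0.05 and 90% power, this is a partial f2 of about 0.035 (about 0.38 residual SD), treating pupils as independent. On the raw-score difference-in-differences scale, it is about 0.44, 0.37 and 0.29 SD for assumed pre-post correlations of 0.3, 0.5 and 0.7.
- Add that, with one school per arm, these figures hold only if there is no school-level variation in change over time. Give no power figures adjusted for an intraclass correlation.

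The cost is one paragraph, with no change to enrolment or analysis. The downside is a less favourable justification: it shows a detectable effect that depends on assumptions, and a caveat about the two schools that sample size cannot remove.
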